**Figure 3 figure3:**
[figure not shown]
Statistical test used in computing the required sample size in G*Power software.

### Participants and Recruitment

The RCT will involve 120 medical students from 2 government-based medical universities: UPM and UKM. These institutions were selected for their convenience and proximity to the researchers. The inclusion of both universities is also intended to account for potential differences in medical curricula and academic schedules between government-based and private medical institutions. Participants will consist of volunteers, specifically undergraduate medical students in the preclinical years (ie, years 1-3). A list of potential participants will be compiled with permission from the dean. Recruitment advertisements will be posted across various platforms, including social media, campus spaces, and noticeboards, to facilitate participant engagement. Before the initial assessment, each participant will be required to complete the consent form and information sheet. Potential participants will undergo a screening process to assess their eligibility before being randomized into either the ISHE or ICBT-I group.

### Randomization and Allocation Concealment

As participants will be recruited from 2 different universities, a stratified randomization method will be used to ensure balance between the groups from each university. Eligible students will be grouped by university and gender before random selection. Gender will serve as a matching factor during the stratified randomization process to ensure a comparable number of female and male students are recruited from both universities.

Data will be collected from volunteer medical students, and the researchers will have no influence on the randomization process or access to future allocations. Each participant will be assigned an identification number and listed before being randomized into either the ISHE or ICBT-I group using online randomization software [34]. A total of 60 students will be allocated to each group.

### Study Location

The initial assessment and experiment will be conducted using a paid Zoom platform. Participants will be interviewed by the researcher using a semistructured questionnaire to determine their eligibility based on the inclusion and exclusion criteria before randomization.

### Eligibility

Upon expressing interest in participating in the RCT, medical students will be directed to a website with general information about the study and its procedures. They will then access the screening assessment document and consent form to complete the eligibility process. After providing informed consent and meeting the inclusion criteria, potential participants will be contacted by phone. During the call, the investigator will confirm the participant’s understanding of the RCT and the provisions for the internet-based interventions being investigated.

The inclusion criteria in Textbox 1 will be considered before recruiting a medical student for this study.

The criteria listed in Textbox 2 will be used to exclude individuals from this study.

Study inclusion criteria.Participants must be aged 18 years or older.Participants must currently be enrolled as medical students in Klang Valley, Selangor, Malaysia.Participants must be willing and able to provide written informed consent.Participants must be able to read and understand English.Participants must have access to reliable internet service, either at university or at home.Participants must be proficient in basic computer and internet operational skills, such as completing self-report questionnaires and online assessments.

Exclusion criteria.Individuals currently suffering from a sleep disorder, such as restless legs syndrome or obstructive sleep apnea [35].Individuals who have previously participated in sleep hygiene programs or undergone cognitive behavioral therapy for insomnia (CBT-I) treatment.Individuals who currently consume alcohol.Individuals with a history or present medical condition that may affect the use of CBT-I, such as recent cardiac surgery, epilepsy (self-reported) within the last 12 months, or currently experiencing an attack of multiple sclerosis.Individuals with tight work schedules, such as night shifts, that may interfere with the completion of the online assessments.Pregnant medical students.Individuals unable to modify their sleep pattern or with limited opportunities to sleep as usual, such as those caring for an infant or having an infant at home.Individuals currently being treated for insomnia and registered in 1 or more trial centers.Individuals suffering from a severe physical health issue requiring surgery or with less than 6 months of prognosis for reassessment.Individuals who have taken prescribed sleeping medication or pills for more than 2 nights in the last 14 days before recruitment into the study.Individuals with suicidal intentions. No other mental or physical health problems will lead to exclusion from this study.

### Blinding

Single blinding will be implemented in this trial. As an online self-report assessment will be conducted, the researchers will remain blinded to the outcomes during the RCT. An automated email will inform the participants of the randomization results, so the medical students will know which group they are assigned to. Limited contact will be maintained between the researchers and participants to prevent any bias in the allocation process or influence on the subsequent assessments. The assessors will remain blinded even after participants contact the research team and reveal their allocation. A researcher (VM; University Putra Malaysia), who has access to all data, will perform the statistical analyses.

### Assessment Points

Participants in both groups will be assessed at baseline (week 0 or pretreatment assessment), week 6, 1 month, 3 months, and 6 months after the intervention. T0 represents the pretreatment assessment, while the subsequent 4 assessment points are designated as T1, T2, T3, and T4, respectively.

### Planned Interventions

#### The Internet Group (CBT-I)

A total of 6 modules focusing on the circadian and homeostatic mechanisms of human sleep regulation and their daytime consequences will comprise the CBT-I, as shown in Table 1. These modules outline the rationale for the key CBT-I interventions: (1) sleep restriction, which involves reducing time in bed to the average self-reported sleep duration from a 1-week sleep diary, plus 30 minutes, with a minimum of 6 hours of sleep and waking up at the same time daily, regardless of sleep duration; (2) stimulus control, which entails not going to bed unless feeling sleepy and not staying in bed unless asleep within 20 minutes; (3) discouraging napping; and (4) cognitive techniques, which involve restructuring dysfunctional beliefs, such as those about the consequences of sleep loss, and targeting unrealistic sleep perceptions or beliefs. A 10-minute video will be used to present the information.

**Table 1 table1:** The structure and contents of the interventions.

Module	ICBT-I^a^ content	ISHE^b^ content
Module 1	Medical students will be introduced to the structure of the intervention and motivation for the therapy. Informing the participants that the treatment of choice for poor sleep quality and sleep disorders is the ICBT-I. Psychoeducation: information about sleep hygiene and regulation.	Medical students will be introduced to the structure of the intervention and motivation for the therapy. Informing the participants that the treatment of choice for poor sleep quality and sleep disorders is the ISHE. Psychoeducation: information about sleep hygiene and regulation.
Module 2	Sleep restriction: reducing time spent in bed, specifically to a minimum of 6 hours, in a stepwise manner. Using the sleep diary completed by the participants since the module to improve sleep pressure. Participants can increase the time spent in bed by 15 minutes if their sleep efficiency is greater than 85%.	Sleep hygiene I (sound, light, and temperature)
Module 3	Sleep hygiene and stimulus control: information on sleep-wake-rhythm, sleep-inhibiting substances, evening rituals, and physical exercise, as well as information on stimulus-control principles aimed at reassociating the bed with sleep.	Sleep hygiene II (food, exercise, and nicotine/alcohol/caffeine)
Module 4	PMR^c^ based on Jacobson [36] with downloadable written instructions and audio.	PMR based on Jacobson with downloadable written instructions and audio tape.
Module 5	Cognitive restructuring: identifying, reexamining, and modifying dysfunctional thoughts and beliefs about sleep and the consequences of poor sleep quality.	Stress management and sleep.
Module 6	Relapse prevention: actions to be taken to prevent poor sleep quality or relapse in sleep perturbations, including when it is appropriate to seek medical assistance and identify the conditions of safe pharmacotherapy.	Treatment evaluation and maintenance.

^a^ICBT-I: internet-based cognitive behavioral therapy for insomnia.

^b^ISHE: internet-delivered sleep hygiene education.

^c^PMR: progressive muscle relaxation.

The program includes a sleep diary in which medical students record their wake time, bedtime, sleep latency, night awakenings, and TST. Graphs will be generated based on the data entered by participants into the sleep diary. Additionally, various exercises will be included to ensure participants practice what they have learned. Participants will have the opportunity to repeat, internalize, and apply the modules, exercises, and examples to their daily lives at their own pace. Behavioral instructions will be provided to guide participants in completing the instruments, sleep diary, and responses during the program’s interactive phase.

Based on the preferred wake-up time and the average TST from the previous week, a sleep window will be proposed. To avoid excessive tiredness, a more flexible minimum time in bed of 6 hours has been chosen for this study. Participants are encouraged to extend their sleep window gradually. Once the sleep diary indicates an SE of 85% or greater over the past week, participants will be advised to add 15 minutes to their sleep window. However, if the recommended SE of 85% is not achieved, participants will be advised to reduce their sleep window based on their preferred average total sleep and wake-up times during the observation period. For those with an SE between 80% and 85%, the sleep window will remain unchanged, but it can be extended by 15 minutes if the efficiency is lower than 85%.

Besides the overall recommendations on sleep hygiene, the medical students will be encouraged to focus on specific behaviors that received the highest scores in the Sleep Hygiene Index (SHI; ie, reducing coffee or alcohol consumption just before bedtime if the participant reports frequent use). They will also be guided by the Dysfunctional Beliefs and Attitudes About Sleep-16 (DBAS-16), particularly for participants who score highly on the item “feel irritable, depressed, or anxious during the day, mostly because I did not sleep well the night before.” This reflects a strong belief in the negative impacts of poor SQ. Such participants will be advised to explore whether there are any underlying reasons for their anxiety and depression, aside from insomnia.

The internet program will serve as the primary medium for delivering all intervention materials, with participants engaging with the materials independently. They will also have the opportunity to consult a clinical psychologist (see the “Withdrawal and Crisis Management Procedure” section). Additionally, participants are strongly encouraged to use the feedback form to contact a specialist, particularly if they are newly recruited into the RCT, experiencing negative effects from the ICBT-I or ISHE interventions, or encountering methodological or technical difficulties with the program. The content of the intervention is entirely based on the well-established ICBT-I, which has been validated and tested in previous studies [37].

Each module will be completed with a homework report, which participants will fill out and submit to their therapists. The therapist will review the report, worksheets, and sleep diary data. Written feedback will be provided within 48 hours, and the therapist will grant the medical student access to the subsequent module. Meanwhile, if the participant is inactive for 1 week, the therapist will be alerted via a mobile phone SMS text message, serving as a reminder and encouragement. If necessary, another SMS text message will be sent, followed by emails, with phone calls as the final step. The therapist (FM) in this study is a licensed clinical psychologist with expertise in poor SQ and insomnia-related CBT.

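### For sleep efficiency from 80% to below 85%, the sleep-window text says reduce, leave unchanged and may extend, and the extension clause contradicts Table 1

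*Protocol article*

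**What the plan says.** The rule for adjusting the sleep window appears in the protocol article under Planned Interventions, The Internet Group (CBT-I), in the running text and in Table 1.

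The running text gives four instructions in close succession:

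- Extend at or above the threshold: "Once the sleep diary indicates an SE of 85% or greater over the past week, participants will be advised to add 15 minutes".
- Reduce below it: "if the recommended SE of 85% is not achieved, participants will be advised to reduce their sleep window". No lower limit of SE is attached.
- Hold in a middle band: "For those with an SE between 80% and 85%, the sleep window will remain unchanged".
- Extend below the threshold, in the same sentence as the hold instruction: "the sleep window will remain unchanged, but it can be extended by 15 minutes if the efficiency is lower than 85" per cent.

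Table 1, Module 2 (ICBT-I column) gives one condition for extension: "Participants can increase the time spent in bed by 15 minutes if their sleep efficiency is greater than 85" per cent.

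Two neighbouring statements are worded loosely. The opening paragraph sets time in bed at average reported sleep "plus 30 minutes, with a minimum of 6 hours of sleep". The later text bases the window on preferred wake-up time and average total sleep time without repeating the 30 minutes, and says that "a more flexible minimum time in bed of 6 hours has been chosen for this study".

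**The concern.** A participant whose diary shows 82% meets the conditions for three different instructions, which point in different directions. This is not a matter of degree or rounding.

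Sleep restriction is the first of four key interventions listed for the ICBT-I arm, and The Internet-Based SHE section names it among the components that the comparator lacks. Psychoeducation, sleep hygiene and progressive muscle relaxation appear in both columns of Table 1, so the contrast between the arms leans on the components that are not shared. If the titration rule has several answers, a reader cannot tell from the article what a participant in this band was meant to do, and delivery cannot be checked against it. Treatment Adherence relies on standardised delivery. The safety section also links sleep restriction to daytime sleepiness and impaired vigilance, so the direction of the adjustment matters to participants.

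**Working it through.** The plan gives no figure to reproduce here. The check is to treat each sentence as a condition on SE and list what it triggers.

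**Conditions**

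- A (running text): SE at or above 85%, add 15 minutes.
- B (running text): SE below 85%, reduce.
- C (running text): SE from 80% to 85%, unchanged.
- D (same sentence as C): SE lower than 85%, may add 15 minutes. Its subject is the 80% to 85% group.
- T (Table 1, Module 2): SE above 85%, may add 15 minutes.

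**Result**

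| Weekly SE | Instructions that apply |
|---|---|
| 75%, 79.9% | B: reduce. D applies only if lifted out of its sentence. |
| 80%, 82%, 84.9% | B: reduce. C: unchanged. D: may extend. |
| exactly 85% | A: extend. C: unchanged, if the band includes its upper end. T: condition for extension not met. |
| 85.1%, 90% | A and T: extend. Consistent. |

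The three-way conflict is confined to SE from 80% to below 85%. In that band D also contradicts T, because the only condition that Table 1 gives for extension is SE above 85%. At exactly 85%, A and T disagree. Above 85% the text is consistent.

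**Illustration.** The documents give no participant data, so these inputs are assumed: 420 minutes in bed, 344 minutes asleep.

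- SE = 344 / 420 × 100 = 81.9%.
- Reduce to average sleep, with the 6-hour minimum: max(360, 344) = 360 minutes. If the 30 minutes are added: max(360, 344 + 30) = 374 minutes.
- Unchanged: 420 minutes.
- Extended: 420 + 15 = 435 minutes.
- Spread: 435 − 374 = 61 minutes to 435 − 360 = 75 minutes.

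For a participant already at the 6-hour minimum, reduce and unchanged give the same window, and the conflict shrinks to keep versus extend.

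**The case against.** The best defence is that a specific sentence after a general one is normally read as an exception: reduce below 80%, hold from 80% to 85%, extend above. That reading is sensible, although the text does not mark the exception. It removes the clash between reduce and unchanged. It does not rescue the final clause, which still allows extension below 85% for the group just told to keep the window, against Table 1.

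Several stronger readings are tempting, and the documents do not support them:

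- *The rule also contradicts itself below 80%.* The extension clause belongs to a sentence about the 80% to 85% group. On the natural reading only reduce applies below 80%.
- *The starting window and the minimum are contradictory too.* The later text does not repeat the 30 minutes but does not exclude them. The phrase about 6 hours of sleep sits in a description of reducing time in bed, and Table 1 and the later text both give 6 hours as time in bed. This is loose wording.
- *Participants received opposite instructions.* The article does not report delivery. It describes a single therapist who reviews diaries and gives written feedback, and it cites treatment and therapist manuals and supervision. The manuals are not shown and may hold one clear rule.
- *ICBT-I is therefore not one defined treatment.* Sleep restriction is one of four listed key interventions, and the fault lies in one SE band of it.

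It is also fair to say that new wording comes late. The Results section reports 48 enrolled in the CBT-I group against 60 planned, with T1 and T2 assessments complete for all participants. A corrected text would reach at most about 60 − 48 = 12 further ICBT-I participants.

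**Conclusion.** The point holds in a narrow form. From 80% to below 85% SE, the running text gives incompatible instructions, its extension clause contradicts Table 1, and text and table differ at exactly 85%. No other part of the article resolves this. Even on the most favourable reading, keep and may extend remain in conflict within one sentence.

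The size for an individual is a window that could differ by about an hour or somewhat more (61 to 75 minutes in the illustration), under the assumed 420 and 344 minutes. The size for the trial is unknown, because the documents do not say how many ICBT-I participants have weekly SE in this band. The arm totals of 60 planned and 48 enrolled are only upper limits.

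Randomisation, the outcome measures and the intention-to-treat comparison are not affected. What suffers is the definition of a component that separates the arms, and the ability to judge fidelity from the article. The conclusion rests on what the article states, not on anything left to the manual.

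**What to change.** The responsible clinicians should reconcile the running text with Table 1, Module 2 into one rule whose SE bands do not overlap and whose boundary at 85% is assigned once. In the same edit, they should state whether the 30 minutes belong to the starting window throughout, and whether the 6-hour minimum refers to sleep or to time in bed. They should then confirm that the treatment manual and the online programme carry that rule. Which rule is right is a clinical decision on which this review takes no position.

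For participants already treated, establish from the existing diaries and the therapist's written feedback, where these have been kept, which instruction was given when SE lay between 80% and 85%, and report it with the fidelity results. If the manual held a single rule all along, saying so settles most of the point.

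The cost is wording in the protocol and, if needed, the manual, with notice to the two ethics committees if they require it, plus a review of existing records. No new data collection is needed.

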#### The Internet-Based SHE

The ISHE modules provide psychoeducation on sleep, insomnia, and goal setting for treatment. The modules cover various topics including sleep hygiene I (light, sound, and temperature), sleep hygiene II (exercise, food, and alcohol/nicotine/caffeine), stress management, applied relaxation, mindfulness, and treatment evaluation and maintenance.

At the end of each module, participants will use a homework report checklist to review their assignments. The research team recommends daily entries in the sleep diary, encouraging participants to explore factors and patterns that affect their sleep. Participants are also encouraged to write comments in the discussion forum for each module and submit a post on a specific theme. While some content in the ISHE overlaps with the CBT-I, it does not include components such as stimulus control, sleep restriction, and cognitive restructuring.

### Treatment Adherence

Treatment adherence will be ensured through a standardized approach to delivering the intervention. The treatment manual outlines the key therapeutic information provided to the medical students, minimizing the influence of individual therapists. Additionally, the use of a therapist manual and supervision will further support adherence to the treatment in both groups.

### Outcome Measures

#### Overview

An email will be sent to participants requesting them to complete the online assessment in a secure online environment [38]. A consistent order of assessments will be followed by each participant at all time points. Participants who fail to complete the outcome measures within 2 days will receive follow-up email reminders. The research instruments consist of 56 items, including the Digital Trail Making Test (dTMT), and should take approximately 20-30 minutes to complete. A recent study demonstrated that online databases can effectively be used for data collection [37]. Participants’ demographic characteristics will be collected only at baseline, including descriptive data on alcohol use and smoking.

#### The Pittsburgh Sleep Quality Index

The Pittsburgh Sleep Quality Index (PSQI) is an instrument used to assess sleep over the previous month, and it is completed at the beginning of 2 study periods. This validated tool, based on polysomnographic research, consists of 19 self-reported items that evaluate 7 components: subjective SQ, sleep duration, sleep disturbance, sleep latency, habitual SE, use of sleeping medications, and issues related to sleep dysfunction. The instrument provides an index score ranging from 0 to 21 points. Scores greater than 5 indicate significant sleep problems, while lower scores reflect high or acceptable SQ [39].

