### Data Analysis

Data will be analyzed using SPSS version 29 (IBM Corp.). Descriptive statistics will be used to obtain information on dropout rates, recruitment, and completeness. All participants will be included in the intention-to-treat analysis for assessing the main efficacy of the intervention, with no planned interim analysis for efficacy or futility. The baseline characteristics of participants will be presented according to their randomized group, with no inferential statistical tests performed at this stage.

For the RCT design, outcome measures will be assessed for normality and presented as either means with SD or medians with IQR, depending on the data distribution. Participants’ characteristics will be summarized using descriptive statistics, with categorical data presented as frequencies and percentages, and continuous data presented as means (SD) or medians (IQR). Normality will be tested using the Kolmogorov-Smirnov and Shapiro-Wilk tests.

Changes in all outcome measures (ie, SOL, TST, NOA, WASO, SQ, SE, dysfunctional beliefs about sleep, presleep arousal, and SHI) from pretreatment (T0) to the first (T1), second (T2), and third (T3) time points will be assessed for treatment effects using repeated measures analysis of variance. Both treatment and time interaction effects will be examined. Paired samples *t* tests will then be conducted within each condition to evaluate possible simple or main effects. Significant findings and statistical trends will be further analyzed using Cohen *d* effect size, which accounts for the correlation between pre- and posttreatment values.

Potential confounding factors, particularly class year and gender, will be addressed and analyzed as variables that may influence the research outcomes. These factors will be incorporated into the analysis through both univariate and multivariate linear regression analyses, allowing for the isolation of each factor and its association with the outcomes of interest.

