Regarding the fourth hypothesis, mediation analyses will be conducted to explore whether changes in the outcome measures from pretreatment to posttreatment are significantly mediated by dysfunctional beliefs and attitudes about sleep, sleep hygiene, and presleep worry. The analysis will follow the traditional mediation model, where the direct, indirect, and total effects are defined in terms of the linear regression coefficients [51]. For example, when the mediation effect size is medium (ie, SM) and the intraclass correlation coefficient is 0.2, with 4 repeated measures, the Sobel method would require 191 participants to achieve 80% power. By contrast, the product-of-coefficients and bootstrap methods would require 188 and 185 participants, respectively, to achieve the same power [52]. This study will adopt the bootstrap method for mediation analysis due to its flexibility in terms of sample size requirements.

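### The week-6 PSQI looks back over treatment, the planned T0–T3 test includes that visit but omits T4, and the mediation visit is unnamed, so neither analysis matches its hypotheses

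*Protocol article*

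**What the plan says.** **Recall and schedule.** The Pittsburgh Sleep Quality Index section says the instrument "is an instrument used to assess sleep over the previous month, and it is completed at the beginning of 2 study periods". No shorter recall period is described for any visit. Assessment Points has participants "assessed at baseline (week 0 or pretreatment assessment), week 6, 1 month, 3 months, and 6 months after the intervention", numbered T0 to T4. The abstract calls the second of these visits post-intervention.

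**What else rests on the PSQI.** Under Other Sleep Measures, the average sleep parameters (SOL, TST, NOA, WASO, SQ, SE) are taken from the PSQI.

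**What happens before T1.** In Table 1, ICBT-I Module 2 is "Sleep restriction: reducing time spent in bed, specifically to a minimum of 6 hours, in a stepwise manner", and cognitive restructuring is Module 5. The Internet-Based SHE section says the comparator contains no sleep restriction, stimulus control or cognitive restructuring.

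**Hypotheses.** Hypotheses 1 to 3 (between-arm efficacy) and hypothesis 4 (mediation) all name T2, T3 and T4. None names T1.

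**Analysis.** Data Analysis tests change "from pretreatment (T0) to the first (T1), second (T2), and third (T3) time points" by repeated measures analysis of variance, followed by paired t tests within each arm. For hypothesis 4 it asks whether "changes in the outcome measures from pretreatment to posttreatment are significantly mediated by dysfunctional beliefs and attitudes about sleep" and the other mediators. No visit number is given there.

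**The concern.** A month-long recall at a visit that closes treatment measures sleep while treatment was running. In one arm only, that period includes deliberate restriction of time in bed, which acts directly on two PSQI components (sleep duration and habitual efficiency) and on the derived TST and SE. The hypotheses concern what remains 1, 3 and 6 months later, yet the planned test takes in the on-treatment visit and leaves out the last follow-up.

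Two conclusions are at stake. A significant group-by-time interaction might be read as support for hypotheses 1 and 3 when it reflects T1 alone. And if the unnamed post-treatment visit in the mediation analysis is T1, the outcome covers the month that ends when the mediators are measured, so the mediator does not precede the outcome.

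**Working it through.** The plan gives no figure of its own on this point to reproduce. The check has four parts.

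**1. The T1 recall window.** Inputs: recall of one month, taken as 28, 30 or 31 days (PSQI section); T1 at week 6 = day 42 (Assessment Points). Week 6 must count from baseline, because it is listed before the visit 1 month after the intervention.
- First day of window = 42 − recall + 1, giving day 15, 13 or 12.
- If treatment fills days 1 to 42 (assumed), 100% of the window is on treatment.
- If treatment ended earlier, with a 30-day recall: end of week 5 gives days 13–35 = 23/30 = 77%; end of week 4 gives days 13–28 = 16/30 = 53%.
- If modules are weekly (also assumed), Module 2 opens on day 8, so every day of the window follows the start of sleep restriction. Module 5 opens on day 29; the share of the window before it is 14/28 = 50%, 16/30 = 53% or 17/31 = 55%.
- T2 is 1 month after the intervention, so its window is roughly the first month after treatment.

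**2. Visits named against visits tested.**

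| Visit | Hypotheses 1–3 | Planned ANOVA | Hypothesis 4 | Mediation analysis |
|---|---|---|---|---|
| T1 | no | yes | no | not stated |
| T2 | yes | yes | yes | not stated |
| T3 | yes | yes | yes | not stated |
| T4 | yes | no | yes | not stated |

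**3. What T1 does to the interaction test.** Let d be the between-arm difference at T0, T1, T2, T3. With equal variances and correlations, the noncentrality of the group-by-time test is proportional to SS = Σ(d − mean d)².
- Equal effect at every post-baseline visit, (0, 1, 1, 1): mean 0.75; SS = 0.5625 + 3 × 0.0625 = 0.75.
- Effect at T1 only, (0, 1, 0, 0): mean 0.25; SS = 0.5625 + 3 × 0.0625 = 0.75.

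The two are identical, so the test cannot tell an effect that vanishes after T1 from one that persists.

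Now hold T2 and T3 at full effect and let T1 show a share k of it (an assumption), profile (0, k, 1, 1):

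| k | Mean effect over T1–T3 = (k + 2)/3 | SS/0.75 |
|---|---|---|
| 1 | 100% | 1.00 |
| 0.75 | 92% | 0.90 |
| 0.50 | 83% | 0.92 |
| 0.25 | 75% | 1.06 |
| 0 | 67% | 1.33 |

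Power is not the issue. With the stated effect size 0.20, correlation 0.5, 56 per group (N = 112) and 4 measurements, the noncentrality at k = 1 is 0.20² × 112 × 4/(1 − 0.5) = 35.84. Even at the lowest ratio in the table, power stays above 99.8%. The interaction can also grow as the T1 effect shrinks, so its size does not track the follow-up effect.

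The planned paired t tests do not repair this: they compare visits within an arm, not arms at a visit.

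**4. Order in the mediation model.** If post-treatment means T1, the mediators are measured at about day 42 and the PSQI outcome covers about days 12–15 to 42. The outcome period ends where the mediator is observed. With mediators at T1 and a PSQI outcome at T2, the outcome period begins at about the time the mediators are measured.

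**The case against.** The best defence is that this is interpretation, not error. Both arms share the same recall window, and restricting time in bed is part of the assigned treatment, so its effect on the T1 PSQI is a legitimate intention-to-treat effect. The abstract also sets the primary outcome as between-group differences after baseline, which takes in T1. This stands: the T1 contrast is valid as an on-treatment comparison, and there is no case for discarding it.

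Stronger readings that a reader might infer are not supported:
- *That the T1 comparison is biased.* It is randomised and symmetric in recall; only its meaning differs.
- *That T1 is the declared mediation outcome.* It is a natural reading, since the abstract labels that visit post-intervention, but Data Analysis gives no visit and hypothesis 4 names T2 to T4. What is documented is a conflict.
- *That some students will be unfinished at week 6.* The phrase "apply the modules, exercises, and examples to their daily lives at their own pace" concerns repeating and using the material. Modules are released by the therapist, with reminders after a week of inactivity. Late completion is possible but not documented.
- *That mediation order fails for every outcome and mediator.* The dTMT is timed at the visit and has no recall period. The Module 5 timing bears mainly on DBAS-16; sleep hygiene is taught in Modules 1 and 3.

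The defence does not answer the mismatch of visits. That would exist with any recall period, and the recall window makes it matter more.

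**Conclusion.** The point holds in a limited form. If treatment runs to about week 6, the T1 PSQI and its derived parameters describe sleep on treatment: all of the window in that case, and 53% to 77% of a 30-day window if treatment ended at week 4 or 5. This rests on assumed pacing, because the article states neither module intervals nor treatment length.

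Two parts need no such assumption. The planned efficacy test covers T0 to T3, while hypotheses 1 to 3 name T2 to T4; one of its three post-baseline visits is unhypothesised, and one hypothesised visit is missing. A significant interaction could come from T1 alone. The mediation analysis names no visit and conflicts with hypothesis 4; if T1 is meant, time order cannot be shown for PSQI-based outcomes. Separately, completing the PSQI at the start of two study periods does not fit five assessments.

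The follow-up data are sound and power is ample. What fails is the link from the planned tests to the stated hypotheses.

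**What to change.** 1. **Efficacy.** Test hypotheses 1 to 3 by between-arm contrasts at T2, T3 and T4. The model may still contain all five visits.
2. **T1.** Keep the T1 PSQI and derived sleep parameters, label them on-treatment, and report them separately. Reconcile this with the abstract's primary outcome by saying which post-baseline visits it covers.
3. **Mediation.** Replace the pretreatment-to-posttreatment wording with mediators (DBAS-16, PSAS, SHI) at T1 and outcomes at T2 or later, as hypothesis 4 requires.
4. **PSQI section.** Replace the two-study-periods statement with T0–T4. State how long treatment lasts, so that a reader can place the T1 window.

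**Cost.** No new visits or data: all five assessments are already scheduled. It is a change to the planned analysis and not only to wording. T1 and T2 data were already collected for the enrolled students, so it should be dated and recorded before any comparison by arm. The trial gives up a confirmatory statement on sleep quality at week 6; no hypothesis makes one, although the abstract's primary outcome would have allowed it.
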